## Abstract

**Background:**

Displaced olecranon fractures after a simple fall are common in elderly patients. This patient group often has multiple medical co-morbidities and low functional demands. Standard treatment for these fractures has been operative fixation, using either wires or a plate. Recent case series suggest that such injuries can be managed without surgery with good functional outcomes. There has been no published trial comparing operative to non-operative treatment for displaced olecranon fractures.

This project aims to test for superiority of operative treatment versus non-operative treatment for displaced olecranon fractures in the elderly, by comparing pain and function in the affected limb up to one year after the injury.

**Methods/Design:**

SOFIE is an international study with a multicentre pragmatic randomised controlled trial design. The primary objective of the study is to compare a patient related outcome, the Disability of the Arm Shoulder and Hand (DASH) Score, between patients treated operatively and non-operatively at twelve months.

Patients will be considered for the study if they are 75 years of age or older, medically fit for surgery, have an isolated displaced olecranon fracture, and present within 14 days of injury. Eligible patients willing to participate will be randomised either to operative fixation, with surgery using the preferred technique of the treating orthopaedic surgeon (tension band wiring or plate fixation), or to non-operative treatment involving early range of motion as tolerated.

Secondary outcome measures will include pain, active range of motion, elbow extension strength, and any adverse events (infection, secondary interventions) at 3 and 12 months.

**Discussion:**

The study will answer an important clinical question about the effectiveness of a commonly performed orthopaedic procedure, and will guide future treatment for displaced olecranon fractures in the elderly.

**Trial registration number:**

World Health Organisation Universal Trial Number (WHO UTN) - U111111574090.

Australian and New Zealand Clinical Trials Registry (ANZCTR) - ACTRN12614000588695.

**Electronic supplementary material:**

The online version of this article (doi:10.1186/s12891-015-0789-6) contains supplementary material, which is available to authorized users.

## Background

The incidence of olecranon fractures in the adult population is 11.5 per 100,000 per year. These fractures make up 20 % of all proximal forearm fractures, and 8–10 % of all elbow fractures. Recent studies have reported an increasing incidence of olecranon fractures in the elderly population [1, 2]. In this age group, they are predominantly fragility fractures seen in patients with multiple co-morbidities and low functional demands [3, 4].

The current standard treatment for displaced olecranon fractures, based on case series and tradition, is operative fixation with either tension band wiring or plate fixation [5–10]. Despite being commonly performed, the results from studies investigating outcomes and complications after operative fixation are conflicting, especially in the elderly with osteoporotic bone. Reported complications include those related to anaesthesia, as well as those specific to the surgical fixation (wire migration, soft- tissue irritation, olecranon bursitis, wire breakage, fracture displacement and the need for a second operation for removal of hardware, with rates as high as 70 %) [11–16].

Further to this high complication rate, there is recent evidence from case series that non-operative management of displaced olecranon fractures is a reasonable option in elderly patients, with comparable outcomes without the risk of anaesthetic and surgical complications [10, 17–19].

Despite extensive case series data, we are unaware of any study directly comparing operative and non-operative management of displaced olecranon fractures in the elderly. The aim of our study is to perform a randomized control trial testing for superiority of operative treatment over non-operative treatment in restoring upper limb function for displaced olecranon fractures in the elderly.

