### Recruitment

Recruitment of patients who meet study eligibility criteria will involve an explanation of the rationale for the study. This will be supplemented with a patient information sheet (see Additional file 1). Patients willing to participate will be asked to sign a consent form. Enrolled patients will then be randomised to either operative or non-operative management by using a central web-based randomisation service. Basic demographic data will be collected for both groups to look at independent variables including age, gender, pre-injury difficulty using arm, comminution (yes/no), diabetes (yes/no), smoking status (current smoker: yes/no) and operation type (wiring or plating) (see Additional file 2). Limited de-identified demographic data (age, gender, hand dominance, residential status) will also be collected on patients who choose not to participate, or are ineligible to participate due to inability to consent. This information will be used to determine selection bias.

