### Outcome measures

Participants will be followed up at two weeks, three months and twelve months post intervention. The primary outcome will be the Disability of the Arm Shoulder and Hand (DASH) Score at 12 months [20]. The DASH score is a widely used, validated outcome tool used in studies of upper limb injuries and surgery, and is a continuous score on a scale from 0 to 100 [21]. Secondary outcome measures collected at 3 months and 12 months will include DASH, EuroQol Visual Analogue Score (EQ VAS), Pain Visual Analgoue Scale (VAS), Mayo Elbow Performance Score (MEPS), complications, elbow active range of motion, and elbow extension strength.

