### Statistical analysis

A two-sided t test will be used to compare the two independent groups. Adjustment for other variables will not be necessary, as the technique of minimisation will be used during randomisation, and randomisation will be stratified by site. Intention to treat analysis will be performed in the primary analysis. As-treated analysis will be added as a secondary analysis. There will be no interim analysis due to the low risk of adverse events compared to usual care and adverse events will be monitored and reported to the administering institution and project manager. De-identified demographic information collected from ineligible or non-consenting patients will be used to understand selection bias in the study.

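### The unadjusted t test on 12-month DASH gives up precision: no pre-injury DASH is listed, and the one pre-injury function item collected has no role in the analysis

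*Protocol article*

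**What the plan says.** - **Aim.** The Background of the protocol article describes a trial "testing for superiority of operative treatment over non-operative treatment in restoring upper limb function". The abstract's Methods/Design paragraph makes this operational as a comparison of DASH "between patients treated operatively and non-operatively at twelve months".
- **Primary outcome.** Under Outcome measures: "The primary outcome will be the Disability of the Arm Shoulder and Hand (DASH) Score at 12 months". DASH is also a secondary outcome at 3 and 12 months. No DASH referring to the time before injury is listed.
- **Baseline data.** The Recruitment section lists "age, gender, pre-injury difficulty using arm, comminution (yes/no), diabetes (yes/no), smoking status", among other items. One of these concerns arm function before the injury. The list is introduced as non-exhaustive and points to Additional file 2, which is not shown.
- **Analysis.** Under Statistical analysis: "A two-sided t test will be used to compare the two independent groups". The same paragraph says that adjustment is not needed, because minimisation will be used and randomisation is stratified by site. Intention to treat is primary, and an as-treated analysis is secondary. No analysis is said to use the pre-injury item.

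**The concern.** Patients are 75 or older, and the Background describes this age group as having multiple co-morbidities. Arm function before the fall will plausibly differ a good deal between them, and part of the spread in 12-month DASH will reflect that rather than treatment. An unadjusted t test leaves all of this spread in the standard error.

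The reason given for not adjusting does not meet the point. Minimisation and stratification make the arms more alike. They do not remove between-patient variance from a t test. Only using the baseline variable in the analysis does that.

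Three things are at stake:

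1. The confidence interval for the primary result is wider than it need be.
2. With about 26 per arm, a chance imbalance in pre-injury function is possible and could not be seen in DASH points.
3. Randomisation does not protect the as-treated comparison, and pre-injury function is an obvious confounder there.

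**Working it through.** **Step 1: reproduce the plan's figure.** Inputs from the Sample size calculation section: difference 15 points, power 95%, significance level 0.05, loss 20%. The test is two-sided (Statistical analysis). The SD is not stated, so I solved for it.

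n per group = 2 × (1.960 + 1.645)² × SD² / 15². With SD = 15 this is 2 × 12.995 = 25.99, so 26 per group. Inflating for loss: 52 / (1 − 0.20) = 65. Both stated figures reproduce. The exact t test gives 94.2% power at 26 per group, close enough to the stated 95%. The stated power is therefore not in question at an SD of about 15.

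**Step 2: precision of the planned analysis.** SE = 15 × √(2/26) = 4.16. With t(50, 0.975) = 2.009, the 95% CI half-width is 8.36 points.

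**Step 3: precision with pre-injury DASH as a covariate.** The half-width is multiplied by √(1 − r²), where r is the within-arm correlation of pre-injury with 12-month DASH. The one degree of freedom lost is ignored. The document gives no r, so a range is shown.

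| Assumed r | √(1 − r²) | Half-width (points) | Narrower by |
|---|---|---|---|
| 0 (planned t test) | 1.000 | 8.4 | – |
| 0.2 | 0.980 | 8.2 | 2% |
| 0.3 | 0.954 | 8.0 | 5% |
| 0.4 | 0.917 | 7.7 | 8% |
| 0.6 | 0.800 | 6.7 | 20% |

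**Step 4: if the SD is larger than the implied 15.** By the normal approximation, unadjusted power at 26 per group is 85% at SD 18 and 77% at SD 20. At SD 20, adjustment gives:

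- r = 0.3: residual SD 20 × 0.954 = 19.1; 15 / (19.1 × 0.277) − 1.96 = 0.87, so power is about 81%.
- r = 0.6: residual SD 20 × 0.8 = 16, so power is 92%.

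**Step 5: chance imbalance.** If pre-injury DASH also had an SD of 15 (an assumption), the difference between arm means would have a standard error of 4.16 points. An imbalance of that size shifts the unadjusted estimate by r × 4.16: 1.2 points at r = 0.3 and 2.5 points at r = 0.6. ANCOVA corrects for this, but the t test does not.

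**The case against.** The strongest reply is that nothing in the primary comparison is invalid. The objective is a between-group difference in DASH at 12 months, and randomisation keeps that unbiased without a baseline score. The design is sized on the unadjusted outcome, and the size reproduces. This stands.

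A reader might infer from the word restoring that the aim cannot be answered without a pre-injury score. The document does not support that. The word occurs only in the Background aim, and no outcome of return to pre-injury level is promised. Under randomisation the expected pre-injury DASH is the same in both arms, so the expected difference in 12-month DASH equals the expected difference in change.

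A reader might also infer that strength and motion should be referred to the uninjured elbow. The article lists "complications, elbow active range of motion, and elbow extension strength" without saying which side is tested, and that is measurement detail an article may leave to forms not shown. An uninjured-side value taken at 3 or 12 months would also be a post-randomisation covariate. Blinded collection is stated only for the 12-month DASH, and the document gives no basis for a side-to-side correlation.

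Two further replies stand in part. Pre-injury function is not ignored, since one item is collected and can show a coarse imbalance. But it has no place in the analysis, and nothing indicates that it is on the DASH scale. The gain is also uncertain: a recalled score may correlate only 0.2 to 0.3 with 12-month DASH, which narrows the interval by 2% to 5%.

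**Conclusion.** The point holds as one about precision and use of baseline information, not about validity. The plan fixes an unadjusted test on a ground that does not justify it, lists no pre-injury score on the outcome scale, and leaves its one pre-injury function item unused.

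The CI half-width would fall from about 8.4 points to between 8.2 (r = 0.2) and 6.7 (r = 0.6). This rests on 26 per arm, the SD of 15 implied by the sample size, and an assumed correlation. The gain is small if r is 0.3 or less, and matters more for power if the SD exceeds 15. No size can be put on confounding in the as-treated analysis. Because Additional file 2 is not shown, a pre-injury DASH may already be collected. In that case only the analysis needs to change.

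**What to change.** 1. At enrolment, before allocation is known, have participants complete the DASH for the week before the injury. If the baseline form already does this, say so.
2. Replace the primary t test with an ANCOVA of 12-month DASH on treatment and pre-injury DASH. Use the score as a covariate and do not analyse simple change: with equal SDs, a change score has lower power than the unadjusted comparison when r is below 0.5 (86% at r = 0.3, against 95% unadjusted).
3. If no pre-injury DASH is available, use the pre-injury difficulty item already collected as the covariate.
4. Include the same covariate in the as-treated analysis, and remove the statement that adjustment is unnecessary.

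The cost is one extra questionnaire at enrolment. Presentation is within 14 days of injury, so the recall period is short. Recall error reduces the gain, but it does not bias the randomised comparison because the score is taken before allocation. A score collected later would not have that protection.

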## Methods and design

SOFIE is a prospective multicentre trial conducted at sites in Australia and New Zealand. The study uses a pragmatic randomised controlled trial design. The study flowchart is provided in Fig. 1.

**Fig. 1 Fig1:**
[figure not shown]
Patient flow through study

### Study population

Patients will be considered for the study if they are 75 years or older, medically fit for surgery, have an isolated displaced (more than 2 mm) olecranon fracture based on standard anteroposterior (AP) and lateral radiographs, and present within 14 days of injury to a participating institution.

Patients will be excluded if they are unable to provide consent due to limited English proficiency or cognitive impairment, have other fractures about the elbow (coronoid, radial head, other ulna or distal humerus fractures), an associated ligamentous injury, a subluxed or dislocated elbow, a flipped fragment (proximal fragment rotates 180° so that the rough trabecular surface of the fracture is in direct contact with overlying skin which can cause skin breakdown), or have an open injury.

### Recruitment

Recruitment of patients who meet study eligibility criteria will involve an explanation of the rationale for the study. This will be supplemented with a patient information sheet (see Additional file 1). Patients willing to participate will be asked to sign a consent form. Enrolled patients will then be randomised to either operative or non-operative management by using a central web-based randomisation service. Basic demographic data will be collected for both groups to look at independent variables including age, gender, pre-injury difficulty using arm, comminution (yes/no), diabetes (yes/no), smoking status (current smoker: yes/no) and operation type (wiring or plating) (see Additional file 2). Limited de-identified demographic data (age, gender, hand dominance, residential status) will also be collected on patients who choose not to participate, or are ineligible to participate due to inability to consent. This information will be used to determine selection bias.

### Randomisation

Consented patients will be randomised to either operative or non-operative management by using a central web-based randomisation service. Randomisation will be stratified by site.

### Interventions

The operative group will undergo surgical fixation by the preferred technique of the treating surgeon (tension band wiring or plate fixation) in a manner consistent with the usual care of the participating institution. The post operative regime will include immobilisation in a long-arm backslab for 2 weeks followed by progressive range of motion as tolerated. This pragmatic approach to surgical intervention more accurately reflects current practice and improves study feasibility and acceptance, and generalisability of the results.

Non-operative treatment will consist of a sling as needed and immediate progressive range of motion as tolerated. A long-arm plaster splint may be applied for the initial 2 weeks if needed for pain control, followed by movement as tolerated. Any decision on referral for physiotherapy will be left to the treating team for both treatment groups.

Study investigators and participants will not be blinded to treatment group. Blinded researchers, however, will collect the primary outcome measure (DASH score at 12 months) via telephone. The statistician will also be blinded to treatment group.

### Outcome measures

Participants will be followed up at two weeks, three months and twelve months post intervention. The primary outcome will be the Disability of the Arm Shoulder and Hand (DASH) Score at 12 months [20]. The DASH score is a widely used, validated outcome tool used in studies of upper limb injuries and surgery, and is a continuous score on a scale from 0 to 100 [21]. Secondary outcome measures collected at 3 months and 12 months will include DASH, EuroQol Visual Analogue Score (EQ VAS), Pain Visual Analgoue Scale (VAS), Mayo Elbow Performance Score (MEPS), complications, elbow active range of motion, and elbow extension strength.

### Sample size calculation

The study will recruit a total of 65 patients with a minimum of 26 in each group at 12 months. This is based on having 95 % power to detect the minimum clinically important difference (15 points) on the DASH score at a significance level of 0.05 and it also allows for 20 % loss to follow up [8, 9, 21].

### Statistical analysis

A two-sided t test will be used to compare the two independent groups. Adjustment for other variables will not be necessary, as the technique of minimisation will be used during randomisation, and randomisation will be stratified by site. Intention to treat analysis will be performed in the primary analysis. As-treated analysis will be added as a secondary analysis. There will be no interim analysis due to the low risk of adverse events compared to usual care and adverse events will be monitored and reported to the administering institution and project manager. De-identified demographic information collected from ineligible or non-consenting patients will be used to understand selection bias in the study.

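### Minimisation and site stratification are given as reasons not to adjust; they are reasons to adjust, and the unadjusted t test is conservative to the extent that the allocation factors predict DASH

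*Protocol article*

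**What the plan says.** The Statistical analysis section of the protocol article fixes the primary comparison: "A two-sided t test will be used to compare the two independent groups". It then rules out covariates: "Adjustment for other variables will not be necessary, as the technique of minimisation will be used during randomisation". In full, two reasons are given, both features of the allocation: "the technique of minimisation will be used during randomisation, and randomisation will be stratified by site". The Randomisation section confirms the second: "Randomisation will be stratified by site". The only further analysis of the comparison is as-treated; no adjusted analysis is mentioned, either as primary or as support.

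The endpoint is continuous: "The primary outcome will be the Disability of the Arm Shoulder and Hand (DASH) Score at 12 months". The Sample size calculation section aims for 65 recruits and at least 26 per group at 12 months, based on "having 95 % power to detect the minimum clinically important difference (15 points) on the DASH score", a significance level of 0.05 and 20% loss. The Recruitment section lists variables to be collected, including "independent variables including age, gender, pre-injury difficulty using arm, comminution (yes/no), diabetes (yes/no), smoking status" and operation type. It does not say which of them, if any, are minimisation factors.

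**The concern.** The article does not merely leave covariates unmentioned. It gives a rule and a reason for it, and the reason points the wrong way.

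Under simple randomisation, chance imbalance in a prognostic factor adds to the variability of the difference in means, and the t test's standard error correctly includes that contribution. Minimisation and stratification suppress the imbalance, so the difference varies less from trial to trial. The t test treats the groups as independent samples and charges for the full outcome variance anyway. Its standard error is then too large unless the balancing factors are in the model.

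What is at stake is precision. With about 52 evaluable patients, a non-significant result would be read through its confidence interval, and the question would be whether a 15-point difference can be excluded. An interval wider than the design warrants weakens that answer.

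**Working it through.** **Inputs from the article.** Difference 15 points, two-sided alpha 0.05, power 95%, 26 per group at 12 months, 65 recruited, 20% loss.

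**Inputs not in the article (assumptions).** The SD of DASH; the share R2 of DASH variance explained by the allocation factors; the number of sites; the minimisation factors and the random element.

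**Step 1: reproduce the sample size and find the implied SD.** n per group = 2 × SD² × (1.960 + 1.645)² / 15². With SD = 15 this is 2 × 3.605² = 25.99, so 26 per group. Total 52; 52 / 0.8 = 65. The stated figures are reproduced, and solving for the SD gives 15.0. With the exact t distribution, power at 26 per group is 94.2%, close to the target. SD = 15 is used below.

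**Step 2: limiting case of perfect balance.** The t test works with SE = 15 × √(2/26) = 4.16. If the balanced factors explain a share R2, the true SE is 4.16 × √(1 − R2). The actual two-sided level is 2 × P(Z > 1.96 / √(1 − R2)), and the interval is too wide by a factor of 1 / √(1 − R2).

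| R2 | Actual level | Interval width ratio |
|---|---|---|
| 0 | 5.0% | 1.00 |
| 0.1 | 3.9% | 1.05 |
| 0.2 | 2.8% | 1.12 |
| 0.3 | 1.9% | 1.20 |
| 0.5 | 0.6% | 1.41 |

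**Step 3: imperfect balance and dropout, by simulation.** 65 patients; minimisation with probability 0.8 on 6 assumed sites and two assumed binary factors, each explaining a third of R2; 20% random loss; total SD 15; 6,000 trials per setting. The t test is compared with a linear model that adjusts for the same factors (site as fixed effects).

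| R2 | Level, t test / adjusted | Mean 95% CI width, t test / adjusted | Power at 15 points, t test / adjusted | Power at 10 points, t test / adjusted |
|---|---|---|---|---|
| 0 | 4.6% / 4.2% | 16.7 / 17.3 | 94.4% / 93.1% | 66% / 63% |
| 0.1 | 4.3% / 4.9% | 16.7 / 16.4 | 94.8% / 94.8% | 66% / 67% |
| 0.3 | 3.2% / 5.0% | 16.7 / 14.5 | 95.4% / 98.1% | 67% / 77% |
| 0.5 | 1.5% / 5.1% | 16.7 / 12.2 | 97.2% / 99.8% | 69% / 89% |

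The Monte Carlo standard error of a level near 3% is about √(0.032 × 0.968 / 6000) = 0.2 percentage points. A separate simulation under the same assumed settings gave t-test levels of 4.3%, 3.3% and 1.7% at R2 of 0.1, 0.3 and 0.5.

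**Step 4: control.** With simple randomisation at R2 = 0.3, the t test's level is 5.3%. The shortfall therefore comes from the restricted allocation that the t test ignores. With no loss to follow-up at R2 = 0.3, the level is 2.1%, close to the limiting 1.9%: random dropout loosens the balance and so softens the effect.

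**The case against.** The strongest defence is that the planned test does no harm. The unadjusted difference remains unbiased, the type I error does not exceed 5%, the interval covers at least nominally, and power at the design difference is about what was planned. All of this stands. The loss is measured against a better analysis, not against the target of 95%.

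It also stands that the size cannot be fixed from the article. At R2 = 0.1 the difference is negligible, and at R2 = 0 adjustment costs a little precision.

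Three stronger readings are tempting and are not supported:

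- **That the trial is left well short of its power.** At 15 points, power of about 77% appears only if the SD is 20 (26 per group, normal approximation). The article gives no such SD, and its own figures imply 15. That fall would come from the larger SD, not from the missing adjustment.
- **That the Randomisation and Statistical analysis sections contradict each other.** Both state site stratification; the second adds minimisation, which the first does not exclude, and the two can be combined. Leaving the minimisation factors unnamed is ordinary condensation in an article. Nor would the stated reason for not adjusting disappear if only site stratification were run, because site stratification is itself part of that reason.
- **That pre-injury difficulty using the arm must be in the model as a stand-in for baseline DASH.** The article does not say how it is measured. Chance imbalance in variables not used in the allocation is already allowed for in the t test's standard error, so it is not a validity problem.

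What survives the defence is that the stated justification is wrong and leads to an analysis that does not match the design.

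**Conclusion.** The point holds in direction and is modest in size. To the extent that site and the minimisation factors predict 12-month DASH, the planned t test is conservative. Over R2 from 0.1 to 0.5, its level falls from about 4.3% to 1.5 to 1.7%. Its interval is wider than the adjusted one by about 2% (16.7 / 16.4), 15% (16.7 / 14.5) and 37% (16.7 / 12.2) at R2 of 0.1, 0.3 and 0.5. Power for 15 points is 0 to 3 percentage points below the adjusted analysis. For a 10-point difference at R2 = 0.3 the gap is about 10 points (67% against 77%). These figures rest on the implied SD of 15 and on assumed sites, factors and R2. False positives are not inflated. This should be fixed, but it does not threaten the validity of the trial.

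**What to change.** Delete the statement that adjustment is unnecessary. Make the primary analysis a linear model of 12-month DASH on allocated arm, by intention to treat, adjusted for the factors used in the allocation: site (as a random intercept, or with small sites pooled) and each minimisation factor by name. Keep the unadjusted t test as a supporting analysis. Do not adjust for operation type, which exists only in the operative arm. One or two strong baseline predictors from those already collected may be added if pre-specified; this is optional.

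The change is to wording only and needs no new data. It uses a few degrees of freedom out of about 50. If the factors turn out not to be prognostic, precision falls slightly: a mean interval width of 17.3 against 16.7 points, and power at 15 points of 93.1% against 94.4%, in the simulated setting with fixed site effects. Pooling small sites or using a random intercept is meant to limit that cost.

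### The reason given for not adjusting does not cover the planned as-treated comparison, which is confounded if crossover is related to prognosis

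*Protocol article*

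**What the plan says.** All the relevant statements are in the protocol article, section Statistical analysis.

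- Test: "A two-sided t test will be used to compare the two independent groups".
- Adjustment: "Adjustment for other variables will not be necessary, as the technique of minimisation will be used during randomisation". The sentence goes on to give stratification by site as a further reason.
- Primary analysis: "Intention to treat analysis will be performed in the primary analysis".
- Secondary analysis: "As-treated analysis will be added as a secondary analysis".

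The article does not define as-treated further, classify a non-operative patient who later has surgery, or give an expected crossover rate. Under Interventions it says that participants and investigators know the treatment group. Under Study population, fitness for surgery is an entry condition: "Patients will be considered for the study if they are 75 years or older, medically fit for surgery".

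**The concern.** An as-treated comparison gives up the protection of randomisation. Balance produced by minimisation and stratification belongs to the allocated groups and is lost when patients are regrouped by what they received. Read together, the sentences support an unadjusted comparison of non-randomised groups, with a justification that does not reach it.

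Prognosis-related crossover is plausible in this setting. The Background section describes fixation as standard treatment and the patients as having multiple co-morbidities, treatment is open, and follow-up lasts 12 months. A non-operative patient who does badly could go on to surgery. A patient allocated to surgery could become unfit after entry. The first would make surgery look worse and the second would make it look better.

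An as-treated analysis is usually added to recover the effect of surgery that crossover dilutes. With about 26 patients per group, three to five selective crossovers are enough to shift it by several points, so a result that differs from intention to treat could reflect selection.

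**Working it through.** **Inputs from the protocol (Sample size calculation):** 26 per group at 12 months; target difference 15 ("the minimum clinically important difference (15 points) on the DASH score"); 95% power; two-sided alpha 0.05; 20% loss.

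**Assumed inputs:** the SD, crossover rate, crossover direction and link with prognosis, none of which the article gives. Higher DASH is taken as worse. Differences are surgery minus non-operative, so positive values go against surgery.

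**1. The plan's own figure.** n per group = 2(1.960 + 1.645)² × SD²/15². With SD = 15 this is 25.99, so 26. Then 52/0.80 = 65. Both stated numbers reproduce with an SD of about 15 (14.7 using the noncentral t), which is the SD used below.

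**2. As-treated bias, one-way crossover, no true effect.** Let the k non-operative patients highest on a prognostic score cross to surgery, where the score has correlation ρ with final DASH. Their mean excess DASH is m = ρ × SD × t, with t the expected mean of the top k of 26 standard normal values. After regrouping, the groups have n + k and n − k patients:

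bias = k·m·[1/(n + k) + 1/(n − k)] = 2n·k·m/(n² − k²)

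| k of 26 | t | m at ρ = 0.5 | bias at ρ = 0.5 | bias at ρ = 0.2 |
|---|---|---|---|---|
| 3 (about 10%) | 1.60 | 12.0 | 2.8 | 1.1 |
| 4 (about 15%) | 1.48 | 11.1 | 3.5 | 1.4 |
| 5 (about 20%) | 1.37 | 10.3 | 4.1 | 1.6 |

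Example for k = 3, ρ = 0.5: 52 × 3 × 12.03/(676 − 9) = 2.8. Simulation agrees at ρ = 0.5 (2.8, 3.5 and 4.0–4.2), with a type I error of roughly 10%, 13% and 15% for the as-treated t test. At ρ = 0.2, simulation gave 1.3 for k = 3 and 1.6 for k = 5.

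**3. When the bias disappears.** With crossover unrelated to prognosis, the simulated bias is 0.0. With prognosis-related crossover in both directions at ρ = 0.5, it is about 0 for 2 + 2 or 3 + 3 patients, and 0.8 for three leaving non-operative care against two leaving surgery.

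**4. A second mechanism.** Suppose a share c of patients in both arms has a prognosis 15 points worse, and those allocated to non-operative care cross to surgery. Bias = 15 × 2c/(1 + c), which is 2.7, 3.9, 5.0 and 6.9 at c = 10, 15, 20 and 30%. Simulation (4,000 trials each) gave 2.6, 3.9, 4.9 and 6.9.

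**5. Does as-treated recover a diluted effect?** Take the mechanism in step 4 with a true effect of −15 and c = 15%:

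- Intention to treat: −15 × 0.85 = −12.75 (simulated −12.8).
- As-treated: −15 + 3.9 = −11.1 (simulated −11.1).
- Complier-average: −12.75/0.85 = −15.0 (simulated −15.1).

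Here as-treated is further from the truth than intention to treat.

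**6. Price and limits of the complier-average estimate.** It divides the intention-to-treat difference by the difference in uptake of surgery, so its spread grows by about 1/(1 − c). Across simulated trials with no true effect, its SD was 5.2 against 4.35 for intention to treat at 15% crossover, and 6.8 against 4.6 at 30%. It also fails if the exclusion restriction fails. Suppose late surgery counts as exposure and failing first adds 10 points to DASH. With no true effect, the error is −10c/(1 − c), which is −1.8 at 15% and −4.3 at 30% (simulated −2.0 and −4.9).

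**The case against.** The strongest defence is that intention to treat is primary, as-treated is only supportive, and the pair is conventional. Nothing in the article rests the trial's conclusion on the as-treated result. This stands, and it limits the point to a secondary analysis.

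A reader might infer that the plan moves failed non-operative patients into the surgical group. The article does not say so. That is the usual meaning of as-treated, but the term could mean initial treatment received, and the definition may sit in a fuller document. A reader might also infer that crossover in this trial will depend on prognosis. No rate, direction or reason is given, and step 3 shows that the bias can be nil. Even the 4-point figure is about one standard error of the difference (15 × √(2/26) = 4.2).

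It can also be argued that the no-adjustment sentence was written for the randomised comparison and leaves the as-treated model open. That is a fair reading, but it concedes that the stated reason does not cover the as-treated comparison, and the article gives no other.

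Finally, a complier-average estimate does not answer the same question free of bias. It targets compliers and needs the exclusion restriction and monotonicity. The first is open to question here because participants are unblinded and DASH is patient-reported. This stands, so the assumptions have to be stated with the estimate.

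**Conclusion.** The point holds in a limited form. The protocol commits to an as-treated secondary analysis, and its only argument against adjustment does not apply to groups formed by treatment received. If crossover is related to prognosis, the unadjusted difference is confounded.

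Under SD 15, correlation 0.5, 10–20% one-way crossover and no true effect, the bias is about 3–4 points against surgery, or 19–27% of the 15-point target. It falls to about 1–1.6 points at correlation 0.2 and to about zero under unrelated or balanced crossover. Selective non-receipt of surgery in the surgical arm would push it the other way. These are conditional illustrations and do not predict the size of the bias in this trial.

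The primary intention-to-treat analysis and the sample size are untouched. The change is worth making because it is cheap and rests on allocation, but it is not needed for the validity of the main result.

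**What to change.** In Statistical analysis:

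1. Confine the no-adjustment statement to the comparison of allocated groups.
2. Make the secondary estimate of the effect of receiving surgery a complier-average effect. Use two-stage least squares with allocated arm as the instrument and initial treatment received as the exposure, defined by a window stated in advance. Count later surgery in a non-operative patient as an outcome of that arm. Late salvage surgery is then not an exposure, which avoids the specific failure shown in step 6.
3. State that the estimate applies to compliers and assumes the exclusion restriction and monotonicity, and note that open treatment with a patient-reported outcome puts the first in question.
4. If an as-treated table is kept, define how crossovers are classified and label it descriptive and non-randomised.

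The cost is wording, plus a record of the initial treatment each patient received. Intervals will be wider than for intention to treat. If 15% of non-operative patients started with surgery, the SD of the estimate would be about 5.2 against 4.35, and at 30% about 6.8 against 4.6. With little initial crossover, the two estimates and their precision would be close.
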